## Abstract

**Background:**

Burns are a global public health problem and cause approximately 180,000 deaths annually, mainly in low- and middle-income countries. Topical antibiotics and occlusive dressing are standard treatments for burns not requiring a skin graft. However, physiotherapy has low-cost phototherapeutic and electrophysical resources (e.g., light-emitting diode [LED]) that may accelerate burn healing. This study aims to compare the re-epithelialization rate of second-degree burns, pain, pruritus, skin temperature, quality of wound healing, and scar quality and mobility among individuals undergoing treatment with red LED, infrared LED, and simulated photobiomodulation.

**Methods:**

This is a double-blinded, three-arm parallel-group, randomized controlled superiority trial. Individuals of both sexes, aged over 18 years, and with second-degree burns will be included. The sample will be divided into three groups of 13 individuals: two will receive LED therapy (red or infrared) and one placebo. Pain, pruritus, skin temperature, and wound size will be assessed daily. Interventions will take place until complete healing, when scar mobility and quality will be evaluated. Data will be presented as mean and 95% confidence interval and analyzed using mixed linear models.

**Discussion:**

This randomized controlled trial has minimal risk of bias and intends to identify the ideal type, procedures, and doses of photobiomodulation to heal burns, which are not standardized in clinical practice. Positive results will allow the implementation of the technique in burn and wound guidelines.

**Trial registration:**

Brazilian Clinical Trials Registry (ReBEC) RBR-8bfznx6. Registered on October 13, 2021

## Administrative information

Note: The numbers in curly brackets in this protocol refer to SPIRIT checklist item numbers. The order of the items has been modified to group similar items (see http://www.equator-network.org/reporting-guidelines/spirit-2013-statement-defining-standard-protocol-items-for-clinical-trials/).

## Introduction

### Background and rationale {6a}

Burns are a global public health problem that causes approximately 180,000 deaths annually, mainly in low- and middle-income countries [1]. The Brazilian government estimates about one million burning accidents per year, of which 2500 evolve to death [2]. Most burned individuals are of working age and generate high financial costs with physical and psychological treatments [3]. Burns heal within 7 to 21 days, depending on depth, patient age, associated diseases, medications, and lifestyle. Open wounds increase the risk of infection and absence from work [4–7].

Improvements in the treatment of severe burns decreased mortality and increased the need for rehabilitation [3, 8, 9]. Although 97% of patients admitted to burn centers survive, non-fatal burns lead to morbidity, psychosocial damage, scar contractures, pruritus, and deformities [10]. In this context, electrophysical resources, such as photobiomodulation, may improve symptoms and functionality during burn healing [11, 12].

Photobiomodulation has been used in animal experiments with promising results. Ideal wavelengths for burn healing are in red and infrared spectra; the former presents better results in cutaneous tissue and the latter in deeper tissues. Energy density ranging from 3 to 6 J/cm^2^ may also be effective for integument healing [13, 14]. Despite this, few clinical trials were published using low-level laser therapy in humans [15–17]. Moreover, only one study analyzed photobiomodulation with a light-emitting diode (LED) of 658 nm for burn healing. The authors included five individuals with bilateral burns (contralateral limb served as a control) and concluded that the limbs on the irradiated side healed faster than the non-irradiated side [14].

Photobiomodulation with LED is a non-invasive, low-cost, and highly viable treatment. Considering the scarcity of studies, we aimed to compare the re-epithelialization of second-degree burns using LED photobiomodulation treatment. We will also compare pain, pruritus, skin temperature, quality of wound healing, and scar quality and mobility among patients receiving treatment with red LED, infrared LED, and simulated photobiomodulation.

### Objectives {7}

#### Research hypothesis

LED will increase the re-epithelialization rate, decrease healing time and pain, and change the local temperature compared with simulated photobiomodulation.

### Study objectives

#### Primary objective

The primary objective is to determine whether LED photobiomodulation is superior to simulation to increase the re-epithelialization rate and decrease the healing time of burn wounds.

#### Secondary objective

The secondary objective is to determine whether LED photobiomodulation is superior to simulation to decrease pain and change the temperature of burn wounds.

### Trial design {8}

This double-blinded, three-arm parallel-group, randomized, controlled, superiority trial (1:1:1) will be performed according to the Standard Protocol Items: Recommendations for Interventional Trials (SPIRIT) (Fig. 1).

**Fig. 1 Fig1:**
[figure not shown]
Study flowchart

## Methods: participants, interventions, and outcomes

### Study setting {9}

The study will be conducted from February 2022 to December 2023. Participants will be referred to the laboratory of the League of Studies in Dermatofunctional Physiotherapy (Department of Physiotherapy, Federal University of Paraíba, Brazil) from urgency and emergency services, basic health units of the city of João Pessoa, and the Hospital de Trauma Senador Humberto Lucena. Evaluations, interview for eligibility, data collection, and application of treatment protocols will also be conducted in the laboratory.

### Eligibility criteria {10}

We will include participants of both sexes who suffered second-degree burns, aged over 18 years, with good mental health (assessed using the Mini-Mental Status Exam) [18], without pre-existing metabolic diseases or infection in injured tissues, not under pharmacological treatment that alters the healing process (e.g., corticosteroids, chemotherapy, or radiotherapy), and who agree to participate in the research by signing the informed consent form.

Participants will be excluded if they develop dermatological diseases or infectious processes or wish to withdraw from the study for bioethical reasons.

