#### Intervention description {11a}

All protocols will be performed using the Endophoton Esthetic Multi equipment (KLD - Brazil), calibrated according to the manual of the manufacturer (Amparo, São Paulo, Brazil). During application in all groups, the researcher and individuals will wear glasses with an eye protection filter for light radiation (suitable for applicators with wavelength between 415 and 904 nm) with minimum attenuation of 95%. The treatment protocol will be performed with individuals in dorsal decubitus and exposing the area to be treated. Photobiomodulation will last until complete re-epithelialization without a predetermined number of sessions, and duration of each session will occur according to wound size.

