#### Strategies to improve adherence to interventions {11c}

Attrition will be considered in case of missing two consecutive or three alternating sessions, inability to complete assessments after treatment and follow-up, and developing any disabling condition preventing the individual from participating in the study. Regarding adherence strategies, flexible schedules will be offered, and participants will be contacted by telephone to confirm evaluation dates. Additional measures to prevent dropouts will also be applied, including periodic assessments of satisfaction with treatment, discussion of difficulties in continuing treatment (e.g., logistics of visits to the laboratory or home care), and attempts to resolve and avoid potential problems affecting adherence. Furthermore, guidance regarding wound care and treatment will also be offered to increase adherence.

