**Fig. 2 Fig2:**
[figure not shown]
Participant timeline

Sociodemographic data, characteristics of the burn (i.e., type of accident, causal agent, and percentage of body surface affected), when the burn happened, and pharmacological treatment received will be registered on an evaluation form. Participants will be instructed to maintain standard care. A trained researcher will assess and perform therapeutic procedures five times a week, once daily. Wound healing rate, pain, pruritus, skin temperature, mobility restriction, and scar quality will be analyzed.

Digital images of the burned area, skin temperature (infrared image), and pain and pruritus will be assessed daily before therapeutic procedures. Only three assessments will be analyzed: initial (before treatment), final (when re-epithelialization of the burn is complete), and one assessment between initial and final assessments (median time of treatment between initial and final assessment). After treatment and total wound closure, mobility and scar quality will be assessed using the adheremeter and Vancouver Scale, respectively.

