## Statistical methods

### Statistical methods for primary and secondary outcomes {20a}

Outcome variables will be re-epithelialization rate, presence and intensity of pain and pruritus, local skin temperature, and scar mobility and quality. Groups will be considered independent variables. Statistical analysis will be performed according to intention-to-treat principles. Descriptive analyses and histogram inspections will determine data normality. Between-group differences and 95% confidence intervals (95% CI) will be calculated using linear mixed models and group, time, and group-versus-time interaction terms. A first-order autoregressive covariance matrix will be considered. Group and time will be considered fixed factors, and participants the random factors. A Q-Q plot will be performed for all variables to consistently and similarly confirm the normality of residues between groups. The SPSS software version 20.0 (IBM SPSS Corp., Armonk, NY) will be used for data analysis.

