### Methods in analysis to handle protocol non-adherence and any statistical methods to handle missing data {20c}

We propose an intention-to-treat analysis considering all participants, regardless of the randomized treatment. The intention-to-treat analysis will be applied using a mixed linear model, which treats missing data randomly.

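### Excluding participants who develop infection or skin disease after entry contradicts the intention-to-treat analysis, and the mixed model cannot repair the loss

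*Protocol article*

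**What the plan says.** All references are to the Protocol article.

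- **Eligibility criteria {10}.** Entry requires participants to be "without pre-existing metabolic diseases or infection in injured tissues". A second paragraph then says: "Participants will be excluded if they develop dermatological diseases or infectious processes or wish to withdraw from the study for bioethical reasons".
- **Statistical methods {20a}.** "Statistical analysis will be performed according to intention-to-treat principles".
- **Non-adherence and missing data {20c}.** "We propose an intention-to-treat analysis considering all participants, regardless of the randomized treatment", followed by: "The intention-to-treat analysis will be applied using a mixed linear model, which treats missing data randomly".
- **Strategies to improve adherence {11c}.** "Attrition will be considered in case of missing two consecutive or three alternating sessions".
- **Intervention description {11a}.** "Photobiomodulation will last until complete re-epithelialization without a predetermined number of sessions". The text under Participant timeline {13} has the researcher "assess and perform therapeutic procedures five times a week, once daily".
- **Participant timeline {13}, on what is analysed.** Although photographs and scores are taken daily, three assessments enter the analysis: before treatment, at complete closure, and one midway between these two.
- **Background {6a}.** Healing takes 7 to 21 days, and a wound that stays open raises the risk of infection and of absence from work.
- **Sample size {14}.** 30 participants are needed, and 39 are recruited to allow for a 30% loss.

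**The concern.** Infection during treatment is an event after entry. Removing a randomized participant because of it conflicts with an analysis of all participants by randomized arm. The exclusion is also unlikely to be unrelated to the outcome. By the article's own account an open wound is at greater risk of infection, and treatment lasts as long as the wound is open, so a slow healer spends longer at risk of being excluded. If infection also differs by arm, the people left in each arm are no longer comparable.

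At stake is the primary comparison itself (re-epithelialization and days to closure) in a trial of 13 per arm, where one or two exclusions can move an arm's mean noticeably.

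**Working it through.** **1. Does the exclusion act after entry?** Infection in the injured tissue is ruled out by the inclusion sentence. The exclusion sentence speaks of developing a condition and, in the same breath, of withdrawing, which only an enrolled person can do. Section {11b} deals separately with stopping or modifying the allocated treatment, so {10} most naturally means leaving the study.

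**2. What remains of an excluded participant?** Of the three analysed assessments, the final one exists only at closure and the middle one is placed by reference to it. A participant removed before closure and not followed has a baseline, neither later assessment, and no observed days to closure. A mixed model valid under missing at random borrows from observed post-baseline values, and this participant has none in the analysed set. In effect the analysis is of completers.

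**3. The plan's own figures.** 30 × 1.3 = 39. The 30 reproduces as a between-groups repeated-measures ANOVA with f = 0.5, three groups, three measurements and α = 0.05, taking a correlation of 0.5 (an assumption; the article gives none): power 0.817. A 30% loss from 39 leaves 39 × 0.7 = 27.3. On the same model power is 0.766 at 27 and 0.917 if all 39 contribute outcomes.

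**4. Infection exclusion: how large and which way?** The article gives no infection rates, so everything here is assumed.

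*Simple arithmetic.* Suppose 2 of 13 in one arm close at day 21 and the other 11 at day 13. The arm mean is (11 × 13 + 2 × 21)/13 = 185/13 = 14.2 days. Excluding the two gives 13.0, a fall of 2 × 8/13 = 1.2 days. If this happens in sham only, the LED benefit looks 1.2 days smaller; in an LED arm only, 1.2 days larger; with the same number and delay in both arms, the difference is unchanged.

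*Simulation.* Healing time is normal with SD 3.5, mean 14 days (sham) or 12 (active), infection adds 5 days, each session is missed with probability 10%, and infected participants and those meeting the missed-session rule are both removed:

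| Daily infection hazard, sham / active | Difference, everyone | Difference, those kept |
|---|---|---|
| 0.01 / 0.01 | 2.08 days | 1.96 days |
| 0.02 / 0.01 | 2.64 days | 1.83 days |
| 0.01 / 0.02 | 1.59 days | 2.10 days |

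**5. Missed-session rule, if it means removal.** Read it as two consecutive misses or three in total, with independent misses at probability p and q = 1 − p. The chance of meeting it in n sessions is

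1 − [qⁿ + n·p·qⁿ⁻¹ + C(n−1, 2)·p²·qⁿ⁻²],

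where C(n−1, 2) counts non-adjacent pairs. For p = 0.10 and n = 5: 1 − [0.5905 + 0.3281 + 6 × 0.01 × 0.729] = 0.038. At five sessions a week, 7, 14 and 21 days are 5, 10 and 15 sessions:

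| Assumed p | 5 sessions | 10 sessions | 15 sessions |
|---|---|---|---|
| 5% | 1.0% | 2.6% | 5.4% |
| 10% | 3.8% | 10.9% | 22.0% |
| 15% | 8.2% | 23.5% | 43.4% |

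A 21-day healer is about five to six times as likely to meet the rule as a 7-day healer. The arm difference nevertheless barely moves. With means of 14 and 9.8 days and SD 2.5 to 4.5, it shrinks by at most about 0.02 days at 5% misses, 0.02 to 0.09 at 10% and 0.06 to 0.20 at 15%. With means of 14 and 12 and SD 3.5, it goes from 2.00 to 1.95 at 15%.

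**The case against.** Five points can be made for the plan.

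- **Missed sessions.** A reader might infer that those who miss sessions are dropped. Section {11c} says only that attrition will be considered, under a heading about adherence. Section {18b} has researchers contact participants to complete follow-up, and {20c} answers non-adherence by including everyone. Removal is an inference from the loss allowance in {14} and the closure-defined assessments in {13}. A loss allowance is also compatible with ordinary missing data. This objection stands: the outright contradiction is confined to {10}.
- **Direction.** A reader might infer that the slower arm always loses its worst courses, so that the LED benefit is understated. The article does not support this. The simulated difference moves either way depending on which arm has more infection, and equal losses with equal delay cancel. This stands.
- **Cause.** Background {6a} says open wounds raise infection risk. It does not say that infection results from slow closure, and {10} speaks of infectious processes generally. The link to healing is plausible, not established. This stands as a limit on wording.
- **Timing.** The first interview precedes randomization, and {10} does not say after randomization. But nothing confines the rule to that window, and treatment continues until closure, so this does not remove the conflict.
- **Wording of {20c}.** A reader might infer that analysis will ignore the randomized arm. The sentence can mean that all participants are kept whichever arm they are in, and {20a} names the principle correctly. This is an editorial fault, not a second design error.

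**Conclusion.** The post-entry exclusion in {10} cannot stand beside the intention-to-treat statements in {20a} and {20c}, and the passages must be reconciled. Because the middle and final analysed assessments depend on closure, the mixed model does not recover participants who leave before it. That conclusion rests on the text alone, with exclusion read as the end of follow-up; no passage says that excluded participants continue to be assessed.

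The size and direction of the bias are not known. They depend on infection rates by arm and on how far infection delays closure. Under the rates assumed above, the shift runs from 0.8 days down (2.64 to 1.83) to 0.5 days up (1.59 to 2.10). The missed-session rule is a conditional and minor part: it selects slower healers, but changes the arm difference by about 0.2 days or less.

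The point should still be settled now. It decides who counts in the primary comparison, recruitment is under way according to Trial status, and photographs that were not taken cannot be recovered.

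**What to change.** 1. Replace the exclusion sentence in {10}: after randomization, no participant is removed from follow-up or analysis because of infection, skin disease or missed sessions.
2. Separate stopping the allocated treatment from leaving the study. When treatment should stop is a clinical matter and is not addressed here. Whatever is decided, photographs and scores continue to closure where the participant agrees, and the participant is analysed in the randomized arm. Withdrawal of consent remains the participant's right; data collected up to that point stay in the analysis as far as consent allows.
3. State in {11c} that the missed-session rule serves only to define a per-protocol set for a sensitivity analysis.
4. As an editorial correction, reword {20c} to say that participants are analysed by randomized group, regardless of treatment received.

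The cost is amendment wording and continued photographs, already taken at treatment visits, for a few participants. The estimate will be diluted somewhat by those who stop treatment early; this is inherent in an intention-to-treat comparison, and the per-protocol set gives a view of it.

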### Who will take informed consent? {26a}

All participants will be informed about the evaluation and treatment procedures during the first interview, which will occur after referral to the laboratory and before randomization. They must sign two versions of the informed consent form to participate (one copy will remain with the participant), following Resolution 466/12 of the National Health Council and the Declaration of Helsinki.

### Additional consent provisions for collection and use of participant data and biological specimens {26b}

By signing the informed consent form, participants will allow us to contact their health professionals to inform them about participation and unexpected findings important to the health of the participant. They will also allow the research team to record one consultation with the health professional, request medical information from their files, and share data with competent authorities if needed. The informed consent form will have an item about the agreement to store and use the personal information of participants for future research. Biological specimens will not be collected for this trial.

### Interventions

#### Explanation for the choice of comparators {6b}

Although LED-sham generates similar sensations to active LED, its different effects will allow verifying whether LED (infrared or red) will affect the re-epithelialization rate. This similarity also ensures the blinding of participants regarding allocation and procedures.

#### Intervention description {11a}

All protocols will be performed using the Endophoton Esthetic Multi equipment (KLD - Brazil), calibrated according to the manual of the manufacturer (Amparo, São Paulo, Brazil). During application in all groups, the researcher and individuals will wear glasses with an eye protection filter for light radiation (suitable for applicators with wavelength between 415 and 904 nm) with minimum attenuation of 95%. The treatment protocol will be performed with individuals in dorsal decubitus and exposing the area to be treated. Photobiomodulation will last until complete re-epithelialization without a predetermined number of sessions, and duration of each session will occur according to wound size.

##### Red light experimental group (RLG)

Red photobiomodulation will be performed using a red LED pen with a wavelength of 658 nm and power of 12 × 40 mW (12 LEDs, each with an energy density of 3 J per point). The pen will be positioned perpendicular to the area to be treated and at the shortest distance without contacting the area. Points receiving therapy will be interspaced by 2 cm.

##### Infrared light experimental group (ILG)

Infrared photobiomodulation will be performed using the LED pen with a wavelength of 858 nm and power of 12 × 50 mW.

##### Sham group (SG)

The equipment will be programmed to emit as little energy as possible (i.e., no therapeutic results).

#### Criteria for discontinuing or modifying allocated interventions {11b}

Participants who present adverse effects due to the intervention protocol, complain of aggravation of the burn wound, or request alteration or withdrawal of the intervention will be discontinued or have their protocols modified.

#### Strategies to improve adherence to interventions {11c}

Attrition will be considered in case of missing two consecutive or three alternating sessions, inability to complete assessments after treatment and follow-up, and developing any disabling condition preventing the individual from participating in the study. Regarding adherence strategies, flexible schedules will be offered, and participants will be contacted by telephone to confirm evaluation dates. Additional measures to prevent dropouts will also be applied, including periodic assessments of satisfaction with treatment, discussion of difficulties in continuing treatment (e.g., logistics of visits to the laboratory or home care), and attempts to resolve and avoid potential problems affecting adherence. Furthermore, guidance regarding wound care and treatment will also be offered to increase adherence.

